### Randomization

Patients are allocated in a 1:1 ratio into the two study arms by stratified block randomization. Randomization procedure is operated centrally via GCP-compliant EDC system. The categorized baseline TWSTRS total score serves as single stratification factor to aim approximately equal distribution of symptom severity in both groups.

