### Statistics

Sample size calculation is based on primary outcome parameter TWSTRS total score change from baseline to FU4. The primary statistical analysis consists in a mean value comparison of the primary outcome between both treatment groups by the independent two-sample T-Test. For sample size calculation we refer to data from previously published studies. A GPi-DBS trial showed a mean therapy effect in TWSTRS total score in patients undergoing neurostimulation of minus 23.1 (±15.2 SD) points [19]. A mean maximum effect of neurotoxin treatment is described with minus 11.0 (±11.7 SD) points on TWSTRS total score at an average of 4 weeks after injection [6]. The resulting standardized mean difference of TWSTRS scores between both groups is 0.90. Using these assumptions a sample size of 2 × 28 = 56 patients ensures a power of 90% to detect this effect size as significant (at significance level 0.05) deviation from the null hypothesis (no difference between mean TWSTRS change scores in DBS and BoNT group). Taking into account a drop-out rate of 15% (conservative estimation) 2 × 33 = 66 must be randomized. Furthermore we assume that 20% of patients will refuse informed consent to undergo DBS after screening and another 20% will fail inclusion criteria of sufficient botulinum treatment response after test injection. Consequently, a total number of 2 × 52 = 104 patients will have to be screened to reach the calculated sample size.

Group comparisons for target variables with sample distributions compatible with the assumption of normality will be conducted by using the two-sided independent sample Student’s T-Test or the paired sample T-Test for within group comparisons (changes between visits). For variables with sample distributions not compatible with the assumption of normality non-parametric tests like Mann-Whitney-Test, Wilcoxon Signed Rank Test or Friedmann Test will be applied. Effects will be considered significant if *p* < 0.05.

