The primary statistical analysis of the primary outcome parameter as well as the secondary outcome parameter change in TWSTRS motor score, TSUI score and SF-36 score will be based on the intention-to-treat (ITT) population. To proof robustness of results two further analyses of sensitivity will be performed: the first one refers to all randomized patients with imputation of missing values after 6 months by appropriate methods of missing-data imputation depending on which missing-data mechanism could be reasonable. The second method includes only patients of per protocol (PP) population.

To address the question how much TWSTRS total score values differ between DBS and BoNT group on average, when patients would be start at baseline with the same score values, we will use ANCOVA (target variable: TWSTRS total change score from baseline to 6 months after operation, main factor: treatment method, covariate: baseline TWSTRS). Thereby we will adjust to imbalances in the TWSTRS distributions at baseline and the variance within the groups should be reduced.

Also for secondary outcome parameters an ANCOVA will be applied using treatment group as main factor, adjusted for each baseline variable as covariate. Furthermore longitudinal data of scores will be analysed by using GEE (generalized estimating equation) and linear models (“mixed models”). This will be helpful to describe interindividual variability of therapy response.

Safety analysis contains a structured list of AE of both study groups. Possibility of relation to study’s interventions will be judged by physicians of the unblinded team. Incidence of AE will be assessed by using Fisher’s Exact Test (analysis by patients: comparisons of proportions of patients with at least one corresponding event) and negative binomial regression (analysis by events: comparisons of counts of occurring events).

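### The primary test is an unadjusted t-test, although randomisation is stratified on baseline TWSTRS and a baseline-adjusted ANCOVA is already planned: valid, but less precise than it could be at no cost

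*Protocol article*

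**What the plan says.** All references are to the protocol article.

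- **Primary test (Statistics).** "The primary statistical analysis consists in a mean value comparison of the primary outcome between both treatment groups by the independent two-sample T-Test". No covariate is named. The variable is the change to FU4: "Sample size calculation is based on primary outcome parameter TWSTRS total score change from baseline to FU4".
- **Sample size (Statistics).** With a standardised difference of 0.90, "a sample size of 2 × 28 = 56 patients ensures a power of 90" per cent at significance level 0.05. Group comparisons are two-sided.
- **Allocation (Randomization).** "The categorized baseline TWSTRS total score serves as single stratification factor".
- **Adjusted analysis (Statistics).** An ANCOVA of TWSTRS total change, with treatment as factor and baseline TWSTRS as covariate, is planned as a further analysis: "Thereby we will adjust to imbalances in the TWSTRS distributions at baseline and the variance within the groups should be reduced". Its time point is given as six months after the operation.
- **General rule on test choice (Statistics).** "For variables with sample distributions not compatible with the assumption of normality non-parametric tests like Mann-Whitney-Test" and others are to be used. The rule does not exempt the primary outcome.

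**The concern.** Change is follow-up minus baseline, so it is correlated with baseline unless the regression slope of follow-up on baseline is exactly 1. Stratifying on baseline balances the arms on that variable and so removes part of the chance variation from the treatment estimate. An unadjusted t-test still counts that variation in its standard error. The reported interval is then wider than it needs to be, and the real type I error falls below 5%.

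The protocol treats baseline TWSTRS as the one variable worth balancing and expects adjustment to reduce variance, but it does not use that gain in the test that decides the trial. All participants have a DBS system implanted, so precision available from data already collected is worth having.

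A smaller matter is the normality rule. It is worded for target variables, and the ANCOVA sentence uses that term for TWSTRS total change. The text therefore leaves open whether the observed distribution could replace the primary comparison of means with a rank test, which addresses a different question.

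**Working it through.** **Inputs from the Statistics section.** DBS change −23.1 (SD 15.2); BoNT change −11.0 (SD 11.7); two-sided 0.05; 28 evaluable per arm; 15% dropout.

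**1. The plan's own figure.** Difference = 23.1 − 11.0 = 12.1. Pooled SD = √((15.2² + 11.7²)/2) = 13.56. Standardised difference d = 12.1/13.56 = 0.892 (0.90 stated). By the noncentral t distribution, 90% power needs 27.4, so 28 per arm. Power at 28 is 90.6% (91.1% at d = 0.90). 56/0.85 = 65.9, so 66. The calculation reproduces.

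**2. ANCOVA at the same sample size.** The correlation rho between baseline and FU4 scores is not given and is assumed. With equal variances at both times:

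Var(ANCOVA)/Var(change) = (1 − rho²)/(2(1 − rho)) = (1 + rho)/2.

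The t-test's 95% half-width is 2.005 × 13.56 × √(2/28) = 7.27 points. The ANCOVA multiplies it by the square root of the variance factor.

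| Assumed rho | Variance factor | Half-width (points) | Power, 28 per arm, 12.1 points | Per arm for 90% power |
|---|---|---|---|---|
| t-test | 1.00 | 7.27 | 90.6% | 28 |
| 0.7 | 0.85 | 6.70 | 94.5% | 24 |
| 0.5 | 0.75 | 6.29 | 96.6% | 21 |
| 0.3 | 0.65 | 5.86 | 98.2% | 19 |

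**3. If equal variances do not hold.** With k = follow-up SD/baseline SD, the factor is k²(1 − rho²)/(1 + k² − 2·rho·k). For rho 0.3, 0.5, 0.7 it is 0.76, 0.87, 0.97 at k = 1.2 and 0.81, 0.91, 0.99 at k = 1.3. In terms of the correlation c between baseline and change, the factor is 1 − c². At c = 0 nothing is gained; at |c| = 0.3 power is 93.0%.

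**4. The t-test under stratified blocks (simulation).** The number of strata and the block size are not given. With 66 patients, tertile strata and equal variances, the null results for rho 0.3, 0.5, 0.7 were as follows (ranges over repeated runs):

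- t-test type I error: 2.2–2.4%, 2.8–3.0%, 3.6–4.3%.
- t-test standard error too large by 16–18%, 10–12%, 5–7%.
- ANCOVA type I error: 4.7–5.2%.

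With 56 patients, two or three strata and c = −0.5 (rho 0.5), t-test power was 92–93% against 96% for ANCOVA. The true gain is thus somewhat below the 90.6% to 96.6% in the table, because stratification already makes the t-test's estimate more stable even though its standard error does not show it. At c = −0.3 the figures were 91–92% and 93%. At c = 0 there was no difference.

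**5. The normality rule.** In the 56-patient simulation with normal data, switching to Mann-Whitney after a Shapiro-Wilk test changed error and power by 0.3 percentage points or less. Mann-Whitney used outright on normal data would have about 89–90% power at 28 per arm.

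**6. Time points.** Table 2 places surgery at week −6 and FU4 at week +24. FU4 is therefore 24 + 6 = 30 weeks after surgery, not six months after it as the ANCOVA sentence says.

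**The case against.** The strongest reply is that nothing here is an error. The t-test after stratified randomisation errs on the safe side, the sample size was calculated for that same test, and the stated power is delivered. All of this stands: the issue is efficiency, not validity.

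The size of the gain is also uncertain. No correlation is given, and equal variances may not hold. Entry has a severity floor (Table 1) and the planning SDs of change differ between arms, so a wider spread at follow-up is plausible. This stands too, and it is why a range including zero is given.

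Three stronger readings are tempting, and the documents do not support them.

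- **That the choice of test leaves the trial underpowered.** A reader might take the 18.3-point DBS effect in the Background, subtract 11.0 and find 51% power at 7.3 points. That questions the planning effect, not the test. The Statistics section plans on 12.1 points, where the t-test has 90.6%.
- **That the primary test will switch with the data.** The Statistics section names the t-test specifically for the primary outcome; the normality rule comes later and is general. Applying the rule to the primary is a fair reading but not an explicit one.
- **That several tests leave the headline result open to choice.** Only one analysis is labelled primary, and the ANCOVA has its own stated question.

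**Conclusion.** The point holds as a recommended improvement. The primary t-test is valid and adequately powered on the plan's own assumptions, but it ignores the only stratification variable, and the protocol already contains the better analysis.

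Under equal variances and rho of 0.3 to 0.7, the ANCOVA variance is 0.65 to 0.85 of the variance that the t-test reports, the interval is about 8 to 19% narrower (1 − √0.85 to 1 − √0.65), and calculated power rises from 90.6% to about 94–98%. With assumed tertile strata the t-test's real type I error is about 2–4%. These sizes rest on assumed values. They shrink to almost nothing if rho is high and follow-up scores are more spread than baseline scores, and to zero if baseline and change are uncorrelated.

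The normality rule needs clarifying, not correcting. Its numerical effect with normal data is negligible.

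**What to change.** 1. Name as primary the ANCOVA of TWSTRS total change from baseline (RAN) to FU4, with treatment as factor and continuous baseline TWSTRS total as covariate. Keep the unadjusted t-test as a sensitivity analysis.
2. Change the ANCOVA's time point in the Statistics section to FU4, so that it matches the variable used for the sample size.
3. State that the primary method is fixed whatever the observed distribution, and that any rank test of the primary outcome is a sensitivity analysis only.

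The cost is a few sentences in the Statistics section, to be settled before unblinding. The model is already planned and TWSTRS is already collected at RAN and FU4. The sample size can stay as it is, since the t-test calculation is the conservative one.

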## Outcome measures

The primary outcome parameter is the difference in TWSTRS total score 6 month after implantation. We hypothesize that under optimized treatment in both groups there should be no discrepancy in symptom severity at FU3 (4 weeks after injection of BoNT at the time of medication’s peak effect).

We defined changes in TWSTRS motor score, TSUI score, CDQ-24 and SF-36 to serve as secondary outcome parameters. Additionally, we measure frequency and severity of spontaneously reported AE in both treatment arms.

Additionally, we will describe the difference in TWSTRS total score between patients of DBS group at FU4 and BoNT group at FU5. At both time points, patients are treated with effective neurostimulation for 6 months, respectively. We suppose the same therapy response of effective DBS in both arms, regardless if the stimulation is applied in a blinded or unblinded fashion.

As other hypothesis we will investigate if the maximum treatment effect of DBS is achieved 6 month after activation. Therefore, we will quantify variations in TSWTRS score in the DBS group 6 and 12 months after randomization.

Motor symptom severity is basically evaluated by using standardized and well-established scales like TWSTRS motor and Tsui score. Tsui includes also a tremor item, which is missing in TWSTRS. Dystonic head tremor is also assessed by the Bain Tremor Rating Scale. Additionally, the severity of dystonia is ranked by patients and physicians using a numeric rating scale (1–10) as element of the Global Clinical Impression (GCI) scale.

Questionnaires referring to pain and disability are also part of TWSTRS total score. Another dystonia-specific tool applied to assess quality of life of patients suffering from cervical dystonia is the Craniocervical Dystonia Questionnaire (CDQ-24). Two further standardized forms supposed to measure general health-related quality of life were chosen to be completed by study participants: SF-36 (Short Form 36) and EQ-5D (Euroquol). To exclude relevant cognitive deficits Mattis Dementia Rating Scale (MDRS) will be applied. Depressive symptoms are assessed by Beck Depression Inventory (BDI). For other psychiatric comorbidities we screen by using the Brief Psychiatric Rating Scale (BPRS).

All scales and questionnaires are used in their German version.

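### As written, the primary ITT t-test implies an available-case analysis at FU4, with all randomised patients entering only through an imputation analysis whose method is left open

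*Protocol article*

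**What the plan says.** All references are to the Protocol article. Under Statistics, the endpoint for sizing is fixed: "Sample size calculation is based on primary outcome parameter TWSTRS total score change from baseline to FU4". The primary test is a "mean value comparison of the primary outcome between both treatment groups by the independent two-sample T-Test". The calculation arrives at 28 patients per arm (56 in all) and then allows for losses: "Taking into account a drop-out rate of 15% (conservative estimation"), which leads to 33 per arm (66 in all) randomised.

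The same section assigns the analysis set. The primary outcome is to be analysed by ITT, and likewise "the secondary outcome parameter change in TWSTRS motor score, TSUI score and SF-36 score will be based on the intention-to-treat (ITT) population". Two further analyses are called sensitivity analyses: "the first one refers to all randomized patients with imputation of missing values after 6 months by appropriate methods of missing-data imputation", and a per-protocol analysis. The imputation method is to be chosen according to whichever missing-data mechanism seems plausible. GEE and mixed models are planned for the longitudinal scores, without primary status. The Abstract also lists the ITT analysis and the imputation-based analysis as separate items. ITT itself is nowhere defined.

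On the secondary outcomes, the Outcome measures section states: "We defined changes in TWSTRS motor score, TSUI score, CDQ-24 and SF-36 to serve as secondary outcome parameters". The ITT sentence under Statistics names three of these four and omits CDQ-24.

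**The concern.** A t-test on the change to FU4 can use only patients who have an FU4 value, unless missing values are filled in first. Here the filling-in, and with it the complete randomised set, belongs to a sensitivity analysis. The natural reading is that the primary analysis is confined to patients observed at FU4 while carrying the ITT label.

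Patients who leave a blinded arm because of poor symptom control or adverse effects need not resemble those who stay, and the reasons may differ between stimulation and toxin. The primary estimate would then be a comparison of selected patients. Table 2 schedules TWSTRS at FU1, FU2 and FU3, so information on patients lost late in the blinded phase would exist but would not enter the primary test.

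The imputation analysis protects less than it could, because its method depends on a later judgement about the missing-data mechanism. Observed data cannot separate missing at random from missing not at random, so that choice should be made before the data are seen.

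**Working it through.** **Inputs** (Statistics section). Mean change under DBS: "minus 23.1 (±15.2 SD) points". Mean change under BoNT: "minus 11.0 (±11.7 SD) points on TWSTRS total score". Evaluable patients: 28 per arm. Planned drop-out: 15%. Randomised: 33 per arm.

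**Step 1: the plan's own figures.** Difference = 23.1 - 11.0 = 12.1 points. Pooled SD = sqrt((15.2² + 11.7²)/2) = 13.56, so the standardised difference is 12.1/13.56 = 0.892. With the simple mean of the two SDs it is 12.1/13.45 = 0.90, the stated value. At 28 per arm and two-sided 0.05, the exact t-test power is 0.906 (at 0.892) to 0.911 (at 0.90). Drop-out: 28/0.85 = 32.9, rounded up to 33 per arm. The stated sample size reproduces. The planned loss is 10/66 = 15.2%.

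**Step 2: what the wording implies.** If the primary t-test already covered every randomised patient with missing FU4 values handled, an imputed analysis of all randomised patients would not be a further analysis. The Abstract makes the same separation. The implied primary analysis is therefore available-case.

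**Step 3: possible bias with balanced drop-out.** Write improvement as positive. Let m = 5/33 = 0.152 be the fraction missing in each arm, and take the planning means as the means of patients observed at FU4. Let a and b be the mean improvements of DBS and BoNT drop-outs; these are assumptions, because the document gives no figures for them. Then

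bias = observed difference - all-randomised difference = m × [(23.1 - a) - (11.0 - b)].

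- Drop-outs resemble completers (a = 23.1, b = 11.0): bias 0, all-randomised difference 12.1.
- All drop-outs unchanged (a = 0, b = 0): 0.152 × 12.1 = +1.8, difference 10.3.
- DBS drop-outs at the BoNT mean, BoNT drop-outs as completers (a = 11.0, b = 11.0): also +1.8, difference 10.3.
- Only DBS drop-outs without benefit (a = 0, b = 11.0): 0.152 × 23.1 = +3.5, difference 8.6. The bias is 3.5/12.1 = 29% of the planned difference.
- Only BoNT drop-outs without benefit (a = 23.1, b = 0): -0.152 × 11.0 = -1.7, difference 13.8.

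**Step 4: more extreme cases.** If all 10 losses fell in the DBS arm (m = 10/33 there), the bias would be 10/33 × 12.1 = +3.7 with drop-outs at the BoNT mean, or 10/33 × 23.1 = +7.0 with drop-outs unchanged. In the other direction, with 5 missing per arm and BoNT drop-outs as completers, the difference reaches zero only if (28/33) × 23.1 + (5/33) × a = 11.0. This gives a = (11.0 - 19.6)/(5/33) = -57, so DBS drop-outs would have to worsen by about 57 points on average.

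**The case against.** The strongest reply is that this is a condensed article. Definitions of analysis sets and detailed missing-data rules commonly sit in the full protocol or the analysis plan, and the imputed analysis might be meant to differ from the primary one only in its handling of missing values. A reader might infer that the primary analysis is certainly a completer analysis under a false name. The document does not support that. ITT is undefined here, the available-case reading is an inference from how the analyses are set against each other, and nothing says that patients who stop treatment go unassessed at FU4.

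The sample size is weak corroboration. Inflating 56 to 66 is routine whatever the analysis set. A reader might also infer that up to 15% of patients can distort the result, but 15% is a planning assumption that the authors call conservative, not a cap, and loss causes bias only if it is related to outcome. The 3.5-point figure is the largest of the balanced scenarios tried, and nothing in the document suggests that drop-outs would fail in one arm only.

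The plan also has safeguards: the imputation analysis covers all randomised patients, and the GEE and mixed models can use earlier visits. All of this stands and limits how far the point can be pressed. It does not remove it, because the article is not silent. It actively gives the all-randomised analysis secondary status and leaves its method open.

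Finally, the CDQ-24 omission cannot bias the primary result. The ANCOVA is stated for secondary outcomes in general, so only the analysis set for CDQ-24 is missing, possibly through an editorial slip.

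**Conclusion.** The point holds as a matter of how the plan is written, and the change should be made. The primary test, as described, implies an available-case comparison at FU4. In the balanced drop-out scenarios the resulting bias runs from -1.7 to +3.5 points on a planned 12.1, and it is nil if those lost resemble those observed. These figures rest on the planning means, on 5 of 33 missing per arm and on assumed outcomes for the missing. They show sensitivity and do not predict bias. At the full planned effect, missing data alone are unlikely to reverse the conclusion. The size of the effect is exposed, and the conclusion would be too if the true effect were smaller. The CDQ-24 discrepancy is a separate, minor wording inconsistency.

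**What to change.** 1. Define ITT as all randomised patients, analysed in the arm to which they were allocated.
2. Make the primary analysis a mixed model for repeated measures on TWSTRS total at FU1 to FU4, with treatment, visit, treatment × visit, baseline and baseline × visit. Visit should be categorical, because the toxin effect varies with time since injection. The treatment difference at FU4 is the primary contrast.
3. This model is valid under missing at random. It corrects for selective drop-out only as far as earlier scores already show it, and patients with no score after baseline add nothing to the contrast. Therefore prespecify one delta-adjusted or reference-based multiple imputation over all randomised patients as the sensitivity analysis, in place of a method chosen later.
4. Keep the observed-case t-test as supportive.
5. Separately, add CDQ-24 to the ITT sentence under Statistics so that it agrees with the Abstract and the Outcome measures section.

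The cost is a change of analysis wording and a somewhat more complex primary model. No new data are needed, since TWSTRS is already scheduled at all four visits and mixed models are already planned. The number randomised stays at 66.
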